#### Control Groups

The control groups will be included in the data collection of laboratory values as well as questionnaires, similar to the intervention group. In addition to this, they will receive the usual care and take part in a minimal intervention in the form of a brochure about self-management of diabetes.

#### Diabetes Specialist Nurses

The study includes DSNs (n=6-10) from the 6 HCCs. DSNs are fundamental to this RCT study because they will take part in introducing and training patients to use the app and recommend individualized self-care support from a website. The training of the nurses will involve learning to use the SMASc questionnaire, to develop the person-centered plan for SMS, and how to train the patients in using a medical software product.

### Outcome Assessments

At baseline and 4 and 12 months’ evaluation, assessments will be conducted. Baseline assessments will involve the collection of demographic data regarding age, gender, marital or family relationships, housing, education, and employment; self-reported outcome measures via questionnaires; and collection of laboratory tests and physical measurements via participants’ medical records. Finally, information regarding diabetes duration, tobacco use, prescribed medication, diet, and exercise habits will be collected. For the follow-up assessments, completion of self-reported outcome measures via questionnaires and collection of laboratory tests and physical measurements via participants’ medical records will be performed.

### Outcome Measures

#### Primary Outcomes

The primary outcome among patients is a change in glycemic control, measured as HbA_1c_ (in mmol/mol) by registered laboratories at baseline and 4 and 12 months’ follow-up. This data will be obtained from patient records. HbA_1c_ levels have been associated with an increased risk of diabetes-related complications. Therefore, the primary outcome in this RCT is the change in HbA_1c_. The main goals of glucose-lowering therapy in T2D are to reduce the risk of diabetes complications while minimizing harms associated with therapy, thus increasing both longevity and health-related QoL.

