### Power Calculation and Sample Size

A power calculation showed that with a sample of 46 participants per group, a power of 80% with an alpha<.05 will demonstrate significant HbA_1c_ difference of 6 mmol/mol between the groups and a within-group SD assumed to be 9 [10]. This means that there is an 80% likelihood that the study will yield a statistically significant effect and allow us to conclude that the mean HbA_1c_ differs between the intervention group versus the control group. To compensate for dropouts, the study needs to enroll 46 participants per group for a total of at least 120 participants.

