### Data Analyses

All analyses to evaluate change over time with regard to intervention outcomes will be made with the intention-to-treat principle, which means that all participants are analyzed according to the group they were randomized into [50]. Appropriate imputation methods will be applied to the missing data.

Baseline and sociodemographic characteristics will be summarized using descriptive statistics. Continuous variables will be summarized as numbers of observed values and mean (SD) or median and quartiles when appropriate. Categorical variables will be described using central tendencies and variability. Differences between groups will be analyzed using inferential statistics.

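### The primary outcome is change in HbA1c, sized with an unlabelled SD of 9 and no stated baseline adjustment; adjusting for baseline HbA1c would gain precision at no cost

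*Protocol article*

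**What the plan says.** Three sections of the protocol article bear on this point.

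- **Primary Outcomes** fixes the variable: "Therefore, the primary outcome in this RCT is the change in HbA_1c". The values are "measured as HbA_1c_ (in mmol/mol) by registered laboratories at baseline and 4 and 12 months’ follow-up", so a baseline value is scheduled for every participant.
- **Power Calculation and Sample Size** gives "a power of 80% with an alpha<.05" for a "significant HbA_1c_ difference of 6 mmol/mol between the groups" and "a within-group SD assumed to be 9". It says the result will "allow us to conclude that the mean HbA_1c_ differs between the intervention group versus the control group". It does not say whether 9 is the SD of HbA1c values or of changes, and it gives no baseline-to-follow-up correlation.
- **Data Analyses** says that change over time is analysed by intention to treat with imputation, and then: "Differences between groups will be analyzed using inferential statistics". No model or covariate is named, and none is ruled out.

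**The concern.** Taken literally, the text leads to a two-group comparison of changes in HbA1c. That comparison subtracts the whole baseline value, whereas the best linear use of baseline subtracts only the fraction that predicts follow-up. The rest adds noise. With 46 per group, some chance imbalance in baseline HbA1c is also plausible, and a model with baseline as covariate handles such an imbalance better than subtraction does.

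The unlabelled SD makes the power statement hard to check. An SD of levels and an SD of changes are equal only when r = .5 (given equal variance at the two visits). If 9 is a level SD and r is low, changes vary more than the calculation assumed, and the claim that "there is an 80% likelihood that the study will yield a statistically significant effect" could fail.

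**Working it through.** **Inputs from the article:** difference 6 mmol/mol, SD 9, alpha .05, power 80%, 46 per group, 1:1 allocation.

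**Assumptions:** two-sided test; individual randomisation; equal HbA1c variance at baseline and follow-up; r not given, so a range of .2 to .9 is shown.

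**Step 1. The article's own figure.** n per group = 2 × (1.960 + 0.842)² × 9² / 6² = 2 × 7.85 × 2.25 = 35.3, so 36 (37 by t-test). Power at 46 per group = Φ(6 / (9 × √(2/46)) − 1.96) = Φ(3.197 − 1.96) = 89.2% (88.6% by t-test). The stated inputs therefore give about 89% at 46 with no dropout, rather than 80%.

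**Step 2. Variance formulas**, with σ the SD of HbA1c levels:

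- change: 2σ²(1 − r)
- adjusted for baseline: σ²(1 − r²)
- ratio, adjusted to change: (1 − r²) / (2(1 − r)) = (1 + r)/2, so the saving is (1 − r)/2

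**Step 3. Power at 46 per group under each meaning of 9** (normal approximation; a t-test gives up to about one percentage point less). Columns 3 and 4 take 9 as the level SD. Column 5 takes 9 as the SD of change, so the adjusted SD is 9√((1+r)/2) and unadjusted power is 89.2% at every r.

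| r | Variance saving | 9 = level: change SD, power | 9 = level: adjusted SD, power | 9 = change: adjusted SD, power |
|---|---|---|---|---|
| .2 | 40% | 11.38, 71.5% | 8.82, 90.4% | 6.97, 98.5% |
| .3 | 35% | 10.65, 77.1% | 8.59, 91.8% | 7.26, 97.8% |
| .4 | 30% | 9.86, 83.1% | 8.25, 93.7% | 7.53, 96.9% |
| .5 | 25% | 9.00, 89.2% | 7.79, 95.8% | 7.79, 95.8% |
| .6 | 20% | 8.05, 94.7% | 7.20, 97.9% | 8.05, 94.7% |
| .7 | 15% | 6.97, 98.5% | 6.43, 99.4% | 8.30, 93.4% |
| .9 | 5% | 4.02, >99.9% | 3.92, >99.9% | 8.77, 90.7% |

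Example, first row: 6 / (11.38 × √(2/46)) − 1.96 = 2.529 − 1.96 = 0.569, and Φ(0.569) = 71.5%.

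**Step 4. Where change-score power crosses 80% if 9 is a level SD.** With 46 per group, 80% power needs an SD of at most 10.27 (normal) or 10.16 (t-test). Setting 9√(2(1 − r)) equal to that limit gives r = 1 − (10.27/9)²/2 = .35, or 1 − (10.16/9)²/2 = .36. Below about .36 the change comparison misses 80%. The adjusted SD cannot exceed 9, so adjusted power cannot fall below the 89% of Step 1.

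**Step 5. Sensitivity to dropout.** The article states no dropout rate. With an assumed 40 analysed per group, the crossing point rises to about r = .45. With 36 analysed, power at SD 9 is 80.7%, so the crossing point is close to r = .5.

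**The case against.** The strongest objection is scope. This is a journal article, and the model and its covariates are commonly left to an analysis plan, which is not shown. That stands: the missing model name is not an error. What remains is what the article does fix, namely an outcome defined as change and a sample size calculation with an unlabelled SD. The source cited beside the SD might explain it, but the sentence itself does not.

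A reader might also infer stronger claims, which the document does not support:

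- **That a raw change-score test is prescribed.** It is not. A baseline-adjusted model, or a mixed model over the visits, fits both the outcome definition and the analysis section.
- **That the trial is powered for one effect and measures another.** Under randomisation, the expected difference in mean change equals the expected difference in mean follow-up HbA1c, so 6 mmol/mol serves both. Only the SD is unclear, and adjustment does not settle what it is.
- **That comparing changes is biased.** Over randomisations it is unbiased. The loss is in precision and in the handling of a chance baseline imbalance.
- **That a definite saving, such as 15% to 30%, can be promised.** That range needs r between .70 and .40, and the article gives no r.
- **That the trial is underpowered.** On the stated inputs, 46 per group gives about 89%. A shortfall needs both a level SD and a low r.

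**Conclusion.** The point holds as a free improvement and a request for clarification, not as a flaw that invalidates the primary comparison. Adjusting for baseline HbA1c is, in large samples, never less efficient than comparing changes. The saving depends on an r that the article does not supply: 40% of the variance at r = .2, 20% at .6 and 5% at .9.

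The effect on the stated 80% power depends on what 9 means. If it is a level SD and all 46 per group are analysed, the change comparison misses 80% only for r under about .36, and the adjusted one stays near 90% or above. If it is the SD of change, power is about 89% without dropout and adjustment adds to a sufficient figure. Dropout moves the crossing point up, as shown. These figures rest on equal variances at the two visits, a two-sided .05 test and individual randomisation.

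**What to change.** - In Data Analyses or the analysis plan, state that follow-up HbA1c (or its change, which gives the same treatment effect once baseline is in the model) is compared between the randomised intervention and control groups. Use a linear model, or a mixed model over months 4 and 12, with baseline HbA1c as a covariate.
- Report the adjusted mean difference in mmol/mol with its 95% CI.
- In Power Calculation and Sample Size, state whether the SD of 9 refers to HbA1c levels or to changes. If it refers to levels, give the correlation assumed.

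The cost is wording. Baseline HbA1c is already collected, and no extra participants, visits or tests are needed. The change should be made before outcome data are examined.

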#### Secondary Outcomes

Secondary outcomes include metabolic measurements, BP, body mass index, waist circumference, and total and high-density lipoprotein cholesterol. Furthermore, lifestyle habits, physical activity, diet, smoking, changes in medical treatment, SMS, diabetes empowerment, diabetes-dependent QoL, improved illness perception, and improved eHealth literacy in the intervention group will be evaluated.

#### Instruments

##### Self-Management Assessment Scale

SMS needs will be measured by SMASc. This 10-item questionnaire has been developed within the research group and measures 5 domains, namely, knowledge, routines, goals, emotional support, and social support, rated on a 6-point Likert scale. Validity and reliability have been tested and found acceptable (manuscript, [name] et al, 2018, unpublished data).

##### Audit of Diabetes-Dependent Quality of Life

Diabetes disease-specific QoL will be measured by the Audit of Diabetes-Dependent Quality of Life (ADDQoL) [34] at baseline and follow-up. This questionnaire measures patients’ perspectives on the impact of diabetes on their QoL in the following 19 domains: leisure activities, working life, journeys, holidays, physical health, family life, friendship and social life, personal relationship, sex life, physical appearance, self-confidence, motivation, people’s reactions, feelings about future, financial situation, living conditions, dependence on others, freedom to eat, and freedom to drink. It consists of 2 overview items, 1 assessing general overall QoL and the other the specific impact of diabetes on QoL [35,36]. Audit of Diabetes-Dependent Quality of Life has been shown to have good validity and reliability in research and practice [35,37]. In this RCT, the Swedish version, SE-ADDQoL, will be used.

##### Brief Illness Perception Questionnaire

Illness perception, measuring cognitive and emotional representations of diabetes, will be assessed using the Brief Illness Perception Questionnaire (IPQ) [38] at baseline and at follow-up. The instrument consists of a 9-item self-reported measure designed to assess cognitive and emotional representations of illness. The Brief IPQ measures concerns, consequences, emotions, identity, illness comprehensibility, personal and treatment control, and the timeline and causes of diabetes. In the Brief IPQ questionnaire, each item is rated using an 11-point Likert scale wherein higher scores indicate greater agreement with the item. The Brief IPQ has been shown to have good reliability and validity in research and practice [38]. In this RCT, the Swedish version, SE-B-IPQ, will be used.

##### European Health Literacy Survey Questionnaire

eHealth literacy will be measured by the shorter Swedish version of the European Health Literacy Survey Questionnaire. The Swedish version of European Health Literacy Survey Questionnaire will be used at baseline and follow-up [39,40]. The instrument consists of 16 items focusing on the following 4 dimensions of health literacy: the ability to access and obtain health information, ability to understand health information (not only in written form), ability to process and appraise health information, and ability to apply and use health information.

##### Electronic Health Literacy Scale

eHealth Literacy will also be measured by the eHealth Literacy Scale (eHEALS) [41]. The 8-item eHEALS scale will be tested and validated to assess consumers’ combined knowledge, comfort, and perceived skills at finding, evaluating, and applying electronic health information to health problems. In this study, a Swedish translated version of the eHEALS will be developed, and its psychometric properties will be tested.

##### Diabetes Empowerment Scale

Diabetes empowerment will be measured by the Diabetes Empowerment Scale (DES) [42]. The short-form Diabetes Empowerment Scale-Short Form, Swedish version will be used at baseline and follow-up. It includes 4 empowerment subscales: goal achievement, self-awareness, stress management, and readiness to change. A 5-point Likert scale is used. Originally, this questionnaire was based on SWE-DES-23, which is considered a valid and reliable tool to assess empowerment in diabetes and rheumatic disease [43,44]. SWE-DES-23 was tested and shortened to become Diabetes Empowerment Scale-Short Form, Swedish version, which was found to be valid and reliable in relation to the original version [43].

##### Intuitive Eating Scale

Eating behaviors will be measured by the Intuitive Eating Scale (IES) [45]. This 21-item scale measures the tendency to follow physical hunger and satiety cues when determining when, what, and how much to eat. In this RCT, the Swedish version, SWE-IES, will be used.

##### Health-related Quality of Life and Cost and Health Economic Evaluation

Health-related QoL and cost and health economic evaluation of the intervention will be measured by the EuroQol 5-Dimensional 5-Level Questionnaire (EQ-5D-5L) at baseline and follow-up. EQ-5D is a generic health-related QoL instrument and a standardized instrument for use as a measure of health outcome [46] from which a single-index value of the respondent’s health status can be derived. EQ-5D is commonly used to estimate the QoL components. Furthermore, it is possible to calculate quality-adjusted life years and thereby perform an economic evaluation of the intervention by means of quality-adjusted life years. It is also used as a health care performance indicator and in the measurement of population health in surveys [47,48]. EQ-5D-5L is a further development of EQ-5D and is based on a health profile consisting of a descriptive system and the EQ visual analog scale. The descriptive system consists of the following 5 dimensions: mobility, self-care, usual activities, pain or discomfort, and anxiety or depression. Each dimension has the following 5 severity levels: no problems, slight problems, moderate problems, severe problems, and extreme problems [49]. In this RCT, the Swedish version, SE-EQ-5D-5L, will be used.

### Data Analyses

All analyses to evaluate change over time with regard to intervention outcomes will be made with the intention-to-treat principle, which means that all participants are analyzed according to the group they were randomized into [50]. Appropriate imputation methods will be applied to the missing data.

Baseline and sociodemographic characteristics will be summarized using descriptive statistics. Continuous variables will be summarized as numbers of observed values and mean (SD) or median and quartiles when appropriate. Categorical variables will be described using central tendencies and variability. Differences between groups will be analyzed using inferential statistics.

### Ethical Considerations

This study will conform to the principles of the declaration of Helsinki [51]. Ethical approval for this trial was granted by the Regional Ethical Review Board at Umeå University (Dnr 2014-179-31M). The major ethical considerations for this study concern the data collection, which might be experienced as tiresome for the participants. However, this risk for the participants is judged as relatively small in comparison with the benefits of receiving person-centered SMS.

## Results

This trial is currently open for recruitment. The anticipated completion date for the study is September 2019.

## Discussion

### Intervention Design

This study protocol describes a planned project aiming to develop and implement an intervention consisting of person-centered, iSMS in primary health care for people with T2D and to evaluate its effectiveness. An intervention like this, in which patients and health care providers are involved in the developmental phase, can lead to more effective SMS and sustainable longer-term effects on health among patients.

The design for this intervention is based on experiences in the research group from previously conducted focus group interviews with primary health care nurses, individual interviews with patients with T2D, a multistakeholder workshop, and results from other studies [19,20,52,53]. Merging current research is beneficial to develop clinically useful interventions based on theory, which could be tailored more specifically for the participants through a cocreative design [54].

Any modifications to the study protocol will be discussed and agreed upon by consensus between the research group before implementing them, and all changes will be documented in a memorandum.

### Conclusions

This study, with its focus on iSMS, will provide insights regarding suitable ways to promote and develop a person-centered intervention regarding the usage of mobile tools. If successful, the intervention has the potential to become a model for the provision of SMS to people with T2D.

## Abbreviations

ADDQoL: Audit of Diabetes-Dependent Quality of Life
BP: blood pressure
DES: Diabetes Empowerment Scale
DSN: diabetes specialist nurse
eHealth: electronic health
eHEALS: eHealth Literacy Scale
EQ-5D-5L: EuroQol 5-Dimensional 5-Level Questionnaire
HbA_1c_: glycated hemoglobin
HCC: health care center
IES: Intuitive Eating Scale
IPQ: Illness Perception Questionnaire
iSMS: interactive self-management support
PCC: person-centered care
QoL: quality of life
RCT: randomized controlled trial
SMASc: Self-Management Assessment Scale
SMS: self-management support
T2D: type 2 diabetes
